## Abstract

**Background:**

People with profound intellectual and multiple disabilities (PIMD) have a combination of severe intellectual disability, extensive physical impairment, sensory impairments and medical health problems. There is, however, a lack of evidence-based physical and health-promoting interventions for people with PIMD.

**Objective:**

Structured Water Dance Intervention (SWAN) is a new method developed to fill this gap. This paper reports a protocol for an intervention study which aims to evaluate SWAN with regard to its effects on physiological, psychological and social health-related variables as well as its cost-effectiveness and potential for implementation in health care.

**Methods:**

The evaluation of SWAN is performed in a multi-center randomized crossover study. Data is collected through cortisol measurement, physiological assessments, proxy ratings, video observations and interviews.

**Conclusions:**

This is the first attempt to evaluate rigorously an innovative intervention for people with PIMD, a group that is rarely considered for health promotion interventions. This study will provide important information about the efficacy, cost-effectiveness and potential to implement SWAN in health care.

What this paper addsThis paper describes the SWAN evaluation study rationale and design, and provide information on the effects and efficacy of SWAN for people with PIMD as well as information on cost effectiveness and on obstacles and enabling factors for the implementation of SWAN in health care settings. The strengths of the study include randomization by minimization to manage participant heterogeneity, the use of multi-methods collecting both quantitative and qualitative data, the use of well-validated data collection methods, cost-effectiveness analyses and interviews with staff and managers to address opportunities and obstacles for the implementation of SWAN. It adds to the need to address people with PIMD and fill the research gap concerning customized interventions. It may be reasonable to assume that people with fewer resources will have similar needs and thus derive similar benefits from SWAN. Thus, if the objectives of the study are reached, it will provide a means to improve the health-related quality of life for people with PIMD, a group with substantial needs.

## Introduction

1

People with profound intellectual and multiple disabilities (PIMD) have a combination of severe intellectual disability and physical impairment, as well as additional sensory impairments, epilepsy or major medical health problems [1]. People with PIMD also have orthopedic complications such as scoliosis and contractures, as well as pain problems that are difficult for staff and relatives to interpret. The causes of PIMD may be chromosomal abnormalities, congenital anomalies, asphyxia, and infection in the fetus or acquired brain injuries resulting from early onset disease or severe accidents. The prevalence of PIMD is low. The most recent figures from Sweden indicate that there were about 80 people per 100,000 inhabitants diagnosed with PIMD in 2010 [2]. In comparison, a study from 2016 carried out in the Netherlands estimated the prevalence there to be approximately 60 per 100,000 inhabitants [3].

Because of the extent of their symptoms, people with PIMD are dependent on personal assistance at all times [2]. Their limited communication capabilities make it difficult for them to convey feelings, thoughts and needs to others, and therefore they have great difficulties in maintaining their integrity and being involved in social interactions [1]. In many countries, people with PIMD are offered some form of organized daily activities. Research in the Netherlands showed that the activities offered can be short and passive in nature and that multiple sensory stimulation is the most popular therapy among activities such as massage, music or warm water pool activities [4]. There is no corresponding overview of the situation in Sweden, but it is reasonable to assume that it is similar.

Floor dance [5] is an activity involving movement to music for people with PIMD. In floor dance, the participant, who is lying on the floor, gets help from staff to move his or her body to music. Floor dance has its roots in dance therapy and is popular and widespread in habilitation centers in Sweden [5]. Floor dance has not been scientifically evaluated, but anecdotal statements from parents and staff testify to its positive effects. Another common activity available to people with PIMD in Sweden is hydrotherapy. Hydrotherapy involves treatments that use the physical properties of water, such as temperature and pressure, for therapeutic purposes [6]. Studies indicate that hydrotherapy can reduce heart rate, reduce pain and decrease anxiety [6], as well as decrease spasticity [7] and stress [8]. In addition, members of staff with experience of hydrotherapy for people with PIMD believe that it is a suitable form of activity for them but that specially designed programs are warranted [9].

### Structured Water Dance Intervention

1.1

Based on the positive experiences of floor dance and hydrotherapy, physiotherapists at the Adult Rehabilitation Center in Örebro, Sweden, combined the advantages of the two methods in what came to be called Structured Water Dance Intervention (SWAN). Using specific body movements equivalent to dance steps, SWAN was designed to give the participants opportunities to enjoy movement and social interaction. By performing dance movements in a warm water pool, synergy effects were expected in terms of reduced spasticity, stress and pain and increased well-being. In 2017, a pilot study was conducted with five persons with PIMD [10]. The results of the pilot indicate that the participants’ spasticity decreased and their level of alertness was slightly increased during the intervention. All participants reached their pre-specified goals, in full or in part, after completing the intervention.

#### Assessment of the project's scientific area of concern

1.1.1

SWAN is a method based on a health promotion and disease prevention approach in accordance with the national guidelines for disease prevention methods issued by the Swedish National Board of Health and Welfare [11]. People with PIMD cannot perform daily physical activity on their own. Because of their extensive disabilities, they are rarely considered for inclusion in various health-promoting initiatives, though they are at high risk of developing health problems. Therefore, it is important that interventions for them are customized, of high quality and evidence-based.

#### Knowledge gaps the project intends to fill

1.1.2

Floor dance and hydrotherapy have been used in the rehabilitation of people with PIMD, but there are to our knowledge no published scientific studies on the effect of these methods on these individuals. To determine whether SWAN, which is inspired by these two methods, is an effective treatment, randomized controlled trials are needed. Using a multiple method approach including objective and subjective measures [12], the SWAN project aims to fill this gap. The knowledge generated in the study can be used by a variety of health service providers in order to implement SWAN for people with PIMD. It is also important to increase our knowledge of the implementation process and facilitate the implementation of evidence-based, cost-effective methods in clinical work. Therefore, the study covers the full intervention research process, from intervention design to implementation [13]. More specifically, the study objectives are:⁃to evaluate the effects of SWAN on health outcomes such as stress, spasticity, alertness, pain, well-being, quality of life and social interaction in people with PIMD.⁃to evaluate the cost-effectiveness of SWAN with respect to changes in healthcare consumption, health status and quality of life.⁃to investigate the opportunities and obstacles with the implementation of SWAN in the healthcare system.

## Methods

2

### Study design

2.1

Since the prevalence of PIMD is very low, we will assess SWAN in a multicenter randomized intervention study enrolling people with PIMD at adult habilitation centers in four Swedish regions. To further increase the study's statistical power, we have applied a crossover design, as shown in Figure 1. At each center there will be two groups: an early intervention group (Group 1) and a late intervention group (Group 2). Group 1 will receive the intervention when they are entered into the study. Group 2 act as a control group and will be instructed to continue with their normal activities. Thereafter, Group 2 will receive the same intervention as Group 1, while Group 1 will be instructed to return to their normal activities. Thus, all participants will complete both control and intervention conditions.

**Figure 1 fig1:**
[figure not shown]
Study flow diagram of the evaluation of the Structured Water Dance Intervention (Background = Demography and physical health variables; Ashworth = Modified Ashworth Scale; EQ-5D = EuroQol five-dimension scale; AR = Assistants ratings; H = Home; C = Centre).

### Study sample

2.2

#### Recruitment and eligibility of study participants

2.2.1

Selection and invitation of the participants will take place locally at each participating center. A licensed physiotherapist at the center selects potential participants based on the following inclusion criteria: (i) having a PIMD, i.e. having a profound intellectual disability (the level of intellectual functioning comparable with an estimated IQ of 20 or below, which in adults corresponds to a mental age below 3 years [14]), as well as having severe sensory and motor impairments corresponding to level IV–V in the Gross Motor Function Classification System [15], (ii) being an adult (18 years or older) and (iii) not finding discomfort with activities in water. Exclusion criteria are: (i) having severe hearing loss (hearing the music is a prerequisite for taking part in the intervention) and (ii) having infections or wounds that will be infectious in the pool. Due to their level of disability, all participants have a legal guardian; before participating in the study, the participant's legal guardian will give written consent after reading written information and being informed by the responsible researchers via telephone or in person.

#### Sample size

2.2.2

Spasticity and cortisol are the primary outcomes of the study. As relevant data on spasticity and cortisol from previous research in the field is lacking, the power analysis is based on available spasticity data from the five persons who participated in the pilot study in 2017. Given that the estimated effect size and standard deviation of the participants in the pilot study are representative of the population, the sample size calculations shows that, with a power of 80% and an alpha of 5%, at least 40 participants are required in order to detect a clinically significant improvement (20%) in estimated spasticity after completed SWAN.

#### Randomization

2.2.3

At each of the four centres, the participants are randomized into the early or late intervention group by minimization [16] based on gender, age and spasticity at baseline, using the MINIM software [17].

### The SWAN program

2.3

#### Multi-disciplinary research team

2.3.1

The research team for this project will consist of members from various disciplinary backgrounds including physiotherapy, psychology, sociology, rehabilitation, dance pedagogy, disability research, speech therapy, health economics, and project management. In addition, each participating center will have a local project administrator who is responsible for all practicalities regarding SWAN at the center.

#### Program design

2.3.2

SWAN is performed as a group activity with 4–5 participants in a warm pool. The SWAN sessions are held once a week for 3 months (12 sessions in total). Each SWAN session takes 40 min and involves a playlist of nine songs. Each song is chosen to stimulate the rhythm of the movements performed, to support relaxation and to emphasize different emotions. Passive movement of different body parts is performed throughout the session. A support person accompanies each participant and functions as a dance partner. The SWAN sessions are led by two SWAN leaders (physiotherapists or assistant physiotherapists). One of them leads the group from the poolside and the other one is in the water to assist the participant and the participant's support person in order to optimize the experience of the activity. Participants use swim collars and other floating devices for an optimal floating position and for safety reasons. A more thorough description of the SWAN method can be found elsewhere [18].

During the study, a physiotherapist in the research team, who is experienced in leading SWAN groups, will be available by phone and e-mail and will also visit each participating center five times for monitoring, to perform measurements and to discuss issues or problems that arise. To ensure that SWAN is implemented in the same way in all participating centers, all SWAN leaders are trained in the theory, method and practice of SWAN. SWAN leaders also receive training in how the measurements are performed and how questionnaires are filled in. Prior to the intervention start, all participants visit the pool with their assistant to become familiar with the facilities and to ensure the working of the assistive devices and other practical support that the participant will need during the intervention.

#### Health economics and implementation

2.3.3

Cost-effectiveness analyses will be carried out in order to give recommendations on how resources should be used to give the greatest health benefits in proportion to the costs of the intervention. Assuming that SWAN shows positive health economic effects, it is of great value to disseminate knowledge on SWAN to health care providers. Therefore, the project will study the implementation process in order to identify impeding and facilitating factors among the participating health care providers. SWAN will adhere to the RE-AIM framework [19] developed to identify systematically the factors that contribute to the implementation and survival of interventions.

### Data collection

2.4

The project uses mixed methods, with both quantitative and qualitative data, to answer the study questions [12]. As shown in Table 1, the project uses a combination of overlapping quantitative measures to obtain reliable evaluations of the intervention effect in combination with interviews with the participants' assistants, SWAN leaders and center managers. The local project manager is responsible for monitoring and collecting the assistant's rating questionnaire after each SWAN session. However, cortisol measurements, video recordings and measurement of spasticity at the first, sixth and twelfth SWAN session as well as the administration of Goal Attainment Scaling (GAS) and interviews with staff and managers will be handled by the research team.

**Table 1 tbl1:** Study variables.

Variable	Data collection methods		
	Direct measurement	Observation	Questionnaires/interviews
Stress	Salivary cortisol		Assistant's ratings
Spasticity	Physiotherapist's assessment		Assistant's ratings
Alertness		Video (facial expression, gaze, movement)	
Pain		Video (facial expression)	Assistant's ratings
Social interaction		Video (facial expression, gaze, movement)	Assistant's ratings
Well-being		Video (facial expression)	Assistant's ratings
Health-related quality of life			EQ-5D
Health economics	Salivary cortisol		EQ-5D and Assistant's ratings
Goal attainment			Goal Attainment Scaling
Experience of SWAN			Interviews with assistants and SWAN leaders
Implementation of SWAN			Interviews with managers

(SWAN = Structured Water Dance Intervention; EQ-5D = EuroQol five-dimension scale).

### Measures

2.5

Demographic and medical data will be collected from the participant's medical records and through interviews with relatives and staff.

#### Primary outcomes

2.5.1

The *Modified Ashworth Scale* [20] is a standardized procedure for measuring the resistance of an extremity in passive motion over a joint, rated on a six-point scale from 0 (no increase in muscle tone) to 5 (limb is rigid in flexion or extension). The scale has high inter-rater reliability [21] and concurrent validity [22], and is appropriate for measuring muscle tone in persons with PIMD [23]. All measurements are performed by the research team physiotherapist and each measurement takes 3–5 min to complete.

*Cortisol* level in saliva will be used as an index of stress [24]. There are no studies on diurnal cortisol of people with PIMD. However, studies on similar populations indicate that diurnal cortisol curves are within the normal range [25]. Thus, a given person tends to have a consistent diurnal rhythm but the cortisol levels may vary across individuals. Therefore, it is important to ensure individual reference points with different stress states [26]. Since cortisol levels tend to peak in the early morning hours and be at their lowest around midnight, measurements will be conducted in the morning when the participants are still in bed and in the evening at bedtime [27]. Cortisol will be measured on 16 occasions during the study (see Table 2), including morning and evening measurements performed at home one week prior to the first SWAN session and at home one week after the last SWAN session. These measurements represent the pre- and post-intervention measurements. During the intervention, cortisol will be measured in connection with the first, sixth and twelfth SWAN session. On these days, the measurements will be made four times [1]: at home in the morning [2], at the pool immediately before entering the pool [3], immediately before the participant leaves the pool after the SWAN session has ended and [4] at home in the evening. This procedure allows us to evaluate whether the SWAN intervention as a whole has an effect on the participants' stress levels (comparing differences from pre-intervention to post-intervention measurements between the intervention and control conditions) and whether the individual SWAN sessions have an effect on the participants’ stress level (comparing poolside measurements before and after the first, sixth and twelfth SWAN session).

**Table 2 tbl2:** Cortisol saliva measurements.

	One week before	Session 1	Session 6	Session 12	One week after
Morning (on waking) at home	IC	IC	IC	IC	IC
Before entering the pool		I	I	I	
Before leaving the pool		I	I	I	
Evening (bedtime) at home	IC	IC	IC	IC	IC

I = intervention group, C = control group.

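### The poolside before/after cortisol comparison has no control-condition samples, so it cannot separate a session effect from the normal daytime fall in cortisol

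*Protocol article*

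**What the plan says.** Section 2.2.2 (Sample size) states that "Spasticity and cortisol are the primary outcomes of the study". The cortisol paragraph of Section 2.5.1 (Primary outcomes) then sets out two comparisons.

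- **Whole intervention:** "comparing differences from pre-intervention to post-intervention measurements between the intervention and control conditions". This is a controlled comparison.
- **Single sessions:** "whether the individual SWAN sessions have an effect on the participants’ stress level", to be answered by "comparing poolside measurements before and after the first, sixth and twelfth SWAN session". No control condition is mentioned.

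Table 2 agrees with the text. Its key is "I = intervention group, C = control group". The home morning and evening rows are marked for both conditions at all five time points. The two pool rows, including "Before leaving the pool", are marked I only.

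The same paragraph says that "cortisol levels tend to peak in the early morning hours and be at their lowest around midnight". It expects this rhythm in the trial population, because "studies on similar populations indicate that diurnal cortisol curves are within the normal range". Section 2.3.2 gives a session length of 40 minutes.

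**The concern.** The single-session question is causal, but the comparison meant to answer it is an uncontrolled change over time. The protocol uses the daily rhythm to time the home samples and states no allowance for it in the poolside comparison. The two pool samples bracket a 40-minute session, so on the protocol's own description the second should tend to be lower whatever happens in the water.

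The expected bias is towards apparent stress reduction. Repeating the comparison at sessions 1, 6 and 12 does not remove it, because each session carries a fall of the same kind, and pooling sessions would only estimate that fall more precisely. A positive finding reported under a primary outcome could not be told apart from time of day. The missing control samples cannot be recovered at the analysis stage.

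**Working it through.** **1. The plan's own figure.** Section 2.5.1 gives 16 cortisol occasions. From Table 2, the intervention condition has 2 (week before) + 3 × 4 (sessions 1, 6, 12) + 2 (week after) = 16, which reproduces. The control condition has 5 × 2 = 10, none of them at pool time. The difference of 6 is exactly the pool samples.

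**2. Inputs for an illustration.**

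- From the documents: gap between pool samples of at least about 40 min (Section 2.3.2); N = 40 and alpha 5% (Section 2.2.2). Two-sided testing is assumed, as the sidedness is not stated.
- Assumed, because the documents give none of these: morning-to-midnight ratio R of 3, 5 or 10; log-linear fall over 17 h; SD of the log before/after change of 0.3 or 0.5.

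**3. Fall with no SWAN effect.** Drift on the log scale: δ = ln(R)/17 × hours. Percentage fall: 1 − exp(−δ).

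| R | δ, 40 min | Fall, 40 min | Fall, 60 min |
|---|---|---|---|
| 3 | 1.099/17 × 0.667 = 0.043 | 4.2% | 6.3% |
| 5 | 1.609/17 × 0.667 = 0.063 | 6.1% | 9.0% |
| 10 | 2.303/17 × 0.667 = 0.090 | 8.6% | 12.7% |

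**4. Chance of a significant reduction when SWAN does nothing.** P = Φ(δ/SE − 1.96), with SE = SD/√n. If the three sessions of a person are fully correlated, n = 40. If they are independent, n = 40 × 3 = 120. These are the two extremes. A valid two-sided 5% test gives 2.5% in this direction.

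| R (40 min) | SD | n = 40 | n = 120 |
|---|---|---|---|
| 3 | 0.5 | 8% | 16% |
| 3 | 0.3 | 15% | 35% |
| 5 | 0.5 | 12% | 28% |
| 5 | 0.3 | 26% | 64% |
| 10 | 0.5 | 21% | 51% |
| 10 | 0.3 | 48% | 91% |

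Example: R = 5, SD = 0.3, n = 40 gives SE = 0.3/√40 = 0.0474, δ/SE = 1.33, and P = Φ(1.33 − 1.96) = 26%.

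**5. With a control.** If the same two samples are taken at matched clock times on control days, the expected null change is −δ in both conditions. The difference is −δ − (−δ) = 0, and the test returns to its nominal level. This assumes that the daily slope is the same on both kinds of day.

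**The case against.** The strongest reply concerns scope. Cortisol is the primary outcome variable, but the documents do not say that the poolside comparison carries the primary efficacy claim. The whole-intervention comparison uses samples taken in both conditions and is untouched. This stands. A reader might infer that the cortisol primary outcome as a whole is uncontrolled; the documents do not support that.

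Second, the text describes a comparison and gives no test or decision rule. Section 2.7 allows time-varying covariates, and clock time could be one. So the documents do not support saying that the fall will necessarily be counted as benefit. The reply goes only part of the way, however. The covariates are optional and none is named. The morning and evening values are two end points that do not give the slope at pool time. No model can supply control samples that were not taken.

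Third, averaging over sessions is not stated in the plan. Comparing the change between sessions 1, 6 and 12 would be largely free of drift if clock times were similar. That is true, but it answers a different question from whether a session has an effect.

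Fourth, the percentages rest on assumed values, and treating 120 session pairs as independent conflicts with the dependency that Section 2.7 recognises. The upper range therefore cannot be read as an estimate, which is why both extremes are shown.

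**Conclusion.** The point holds for the second cortisol comparison only. As written, it cannot distinguish an effect of the session from time of day, and the expected direction of the bias, towards apparent stress reduction, follows from the protocol's own account of the daily rhythm.

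The size is unknown. Under the assumptions shown, the null fall over 40 minutes is about 4% to 9%, and the chance of a false reduction is about 8% to 48% with fully correlated sessions or 16% to 91% with independent ones, against 2.5%. These figures illustrate the problem and do not predict this trial's error rate. The local slope depends on the shape of the curve and on the clock times of the sessions, and the article gives neither.

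**What to change.** **Minimum.** In the cortisol paragraph of Section 2.5.1, state that the clock times of the pool samples are recorded, that the poolside before/after change is descriptive and outside the primary outcome, and that no causal conclusion about session effects on stress is drawn from it. Base the cortisol conclusion on the controlled whole-intervention comparison. The cost is a change of wording and a recorded time for each sample.

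**Preferable, if the added collection burden is acceptable.** On the three control days that already have home samples, take two further saliva samples at clock times matched to the pool samples. Test the SWAN-day change minus the control-day change within person. This adds 2 × 3 = 6 tubes per participant, or 6 × 40 = 240 at N = 40, and raises the control condition from 10 to 16 samples. The burden is real: the article does not say who takes the home samples, and daytime samples may fall away from home, whereas Section 2.6.1 describes storage in the home freezer.

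Predicting the fall from the morning and evening values and subtracting it is not an adequate substitute, because two end points do not determine the slope at pool time.
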